### Methods to Address Potential Sources of Bias

This study, given its retrospective nature, is potentially affected by a series of biases, whose prevention or compensation will be attempted through various techniques. The 3 most important biases are discussed below:

Reverse causality bias: drugs that are prescribed to patients near death to control their symptoms will appear associated with an increased risk of death in the analyses, with the prescription of these drugs not being the cause of death but a consequence of proximity to death. This bias will be alleviated by eliminating the drugs prescribed 3 months before death from the analysis.“Immortal patient” bias: the longer a patient survives, the more likely he or she is to be diagnosed with pathologies and to consume drugs. This can give the false appearance that the drugs consumed throughout life are the cause of prolonged survival. To control this effect, the analyses only considered the drugs consumed up to a certain date in the group of patients who survived until that same date. For example, in the group of patients who have survived at least 3 months after the diagnosis of their cancer, only drugs consumed at any time up to month 3 after the cancer diagnosis will be considered. Thus, the consumption of the drug will not be explained by longer survival because the entire group will have survived until the moment when the drugs under study are consumed. Patients who consume the study drugs after the established time cutoff point will be eliminated from the analysis. As a comparison group, only patients who have not consumed the drug at any point in their disease evolution will be taken into account.Diagnostic anticipation or “medical surveillance” bias: this bias occurs when patients are included in studies who are in a screening program for cancer because, in such programs, the cancer is diagnosed earlier, which causes the erroneous impression that the individuals live longer. In our database, patients with certain diseases may have undergone frequent diagnostic tests, thus triggering early cancer detection. For example, patients with chronic obstructive pulmonary disease (COPD) may have undergone periodic radiographs, in which lung cancer has been detected early. This may give the impression that COPD, or the drugs used by patients with COPD, are associated with increased survival from lung cancer. To control this bias, patients with a previous pathology that produces greater medical surveillance of the organ where the cancer developed will be eliminated from the analysis.

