### Statistical Analysis

To achieve the primary objective, several exploratory analyses will be performed. These will look for an association between the use of the different drugs available in the database (the exposure variable) and patient survival (the outcome variable). The exposure variable will be treated both dichotomously (exposed or not exposed) and quantitatively. The time exposed to the drug, the average monthly dose, the maximum dose, or the cumulative dose per unit of time will be considered. Specific analyses will be carried out on the effect of 2 or more drugs that have been shown to influence survival when they have been consumed, either simultaneously or sequentially, within the time unit being analyzed. The outcome variable is survival during the observation period. Patients who are censored, for whom no death is recorded during the follow-up time, are considered alive at the end of the period.

In addition to the machine-learning techniques described above, the association between exposure and outcome will be investigated using 2 different approaches. The exposure odds for each drug will be calculated, and this exposure will be compared between patients considered alive at 5 years and those who have died using odds ratios (exposure odds ratio). The group of nonsurvivors will be selected with different time criteria in a sensitivity analysis: deceased in the 1st, 2nd, or 3rd year after diagnosis. Second, the survival time of participants exposed and unexposed to each drug available in the database (individual agents, ATC5 codes) or to each family of agents (ATC4 codes) will be compared.

To avoid bias due to a lack of randomization, in both approaches, matching will be carried out between the groups with respect to confounding variables. In addition, if residual confounding is suspected or an imbalance between groups remains after matching, adjustments for age, sex, and diagnostic groups will be performed. A Cox regression model will be constructed to estimate the effect of the evaluated drug. The hazard ratio (HR) and its 95% CI will be reported. Hazard proportionality will be assessed graphically by Schoenfeld residuals.

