
### Sample Size Considerations

Based on a maximum 5-year survival probability of 20% (P=.2, *Q*=.8) and with a significance level of 5% (95% CI) and a power of 80%, it will be possible to detect a difference of 10% between 2 groups with 294 individuals per group. Table 2 shows an initial estimate of the number of survivors at 5 years available during the study period. According to preliminary data not shown, the database available for the study includes a total of 102,860 patients diagnosed with the cancers under study.

**Table 2 table2:** Incidence and estimated survival for the main pathologies under study.

Cancer	New cases each year, n	Estimated 5-year survival, n (%)	Cumulative survivors throughout the study, n
Lung	4079	738 (18.1)	3691
Metastatic colon	6128	852 (13.9)	4259
Metastatic bladder	2444	122 (5)	611
Metastatic kidney	1094	131 (12)	656
Metastatic melanoma	860	171 (19.9)	856
Pancreas	1168	96 (8.2)	479
Esophagus	616	116 (18.8)	579
Metastatic stomach	1089	57 (5.2)	283
Liver	670	118 (17.6)	590

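### Removing prescriptions from the 3 months before death edits exposure only in patients who die, which tilts a drug with no effect towards looking protective; an equal lag for everyone would not

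*Protocol article*

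**What the plan says.** Three rules in the protocol article act together.

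- **Reverse causality** (Methods to Address Potential Sources of Bias): "This bias will be alleviated by eliminating the drugs prescribed 3 months before death from the analysis".
- **Immortal time** (same section): exposure is fixed at a landmark in patients alive at that date. In the example given, "only drugs consumed at any time up to month 3 after the cancer diagnosis will be considered". Month 3 is an illustration, not a fixed choice. The comparator is restricted: "As a comparison group, only patients who have not consumed the drug at any point in their disease evolution will be taken into account".
- **Comparison** (Statistical Analysis): "this exposure will be compared between patients considered alive at 5 years and those who have died using odds ratios", with nonsurvivors also taken as those "deceased in the 1st, 2nd, or 3rd year after diagnosis" in a sensitivity analysis. In the second approach, "A Cox regression model will be constructed to estimate the effect of the evaluated drug". On the scale of exposure: "The exposure variable will be treated both dichotomously (exposed or not exposed) and quantitatively".

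The Statistical Analysis section also sets P=.05 without correction and discards findings reproduced in the cancer-free controls. The Discussion admits a residual effect of the reverse-causality and immortal-time biases, but does not mention that the deletion depends on the outcome.

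**The concern.** Only a patient with a death date can lose prescriptions under this rule. Take the month-3 example. A patient who dies at month 4 keeps prescriptions from month 1 only. A patient who dies just after month 3 keeps almost none. A patient alive at month 6 keeps all three months. Exposed early deaths therefore leave the exposed group, and nothing comparable happens to survivors. The misclassification depends on the outcome, and for drugs started within the exposure window it favours the drug.

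The study looks for drugs linked to longer survival, which is the direction of this artefact. A small systematic shift, applied to many drugs in a database of 102,860 patients, can become a list of false candidates for repurposing.

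**Working it through.** **The plan's own figures.** The protocol gives no figure for this bias. Its one related calculation, 294 per group for 20% versus 30% survival, is correct and unaffected: (1.960·√(2·0.25·0.75) + 0.842·√(0.16+0.21))² / 0.10² = 293.2, rounded up to 294.

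**Inputs from the protocol.** 5-year survival of 20% ("Based on a maximum 5-year survival probability of 20"%) and 5% (metastatic bladder, Table 2); the month-3 landmark example; the 3-month deletion.

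**Assumptions not in the protocol.** Constant hazard; a drug with no effect; 20% of patients exposed by month 3; starts spread evenly over months 0-3.

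**Step 1: exposed deaths that lose their exposure.** Hazard h = −ln(S5)/60, which is 0.0268 per month at 20% and 0.0499 at 5%. Only deaths in months 3-6 can lose a start made in months 0-3, and about half of them do. Among patients alive at month 3:

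| | S5 = 20% | S5 = 5% |
|---|---|---|
| Die in months 3-6: 1 − e^(−3h) | 0.0773 | 0.1391 |
| Die in months 3-12: 1 − e^(−9h) | 0.2145 | 0.3620 |
| Die in months 3-60: 1 − e^(−57h) | 0.7832 | 0.9419 |
| Exposure lost, all deaths | 0.5·0.0773/0.7832 = 4.9% | 0.5·0.1391/0.9419 = 7.4% |
| Exposure lost, year-1 deaths | 0.5·0.0773/0.2145 = 18.0% | 0.5·0.1391/0.3620 = 19.2% |

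**Step 2: approximate hazard ratio.** If affected patients are dropped, exposed deaths fall by the share lost: 1 − 0.049 = 0.95 and 1 − 0.074 = 0.93. If they are recoded, unexposed deaths also rise by 0.25 times that share: 0.951/1.012 = 0.94 and 0.926/1.018 = 0.91. The small change in person-time is ignored.

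**Step 3: odds ratio, 5-year survivors versus year-1 deaths.** Survivors' odds of exposure are 0.2/0.8 = 0.25. Recoded decedents at S5 = 20%: 0.2·0.820/(0.8 + 0.2·0.180) = 0.196, so OR = 0.25/0.196 = 1.27. Dropped: 0.2·0.820/0.8 = 0.205, OR = 1.22. At S5 = 5% the values are 1.30 and 1.24.

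**Step 4: simulation of the full rules, no drug effect, month-3 landmark, new starts.**

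| | S5 = 20% | S5 = 5% |
|---|---|---|
| HR, no deletion | 1.00 | 1.00 |
| HR, deletion, recoded | 0.94 | 0.91 |
| HR, deletion, dropped | 0.95 | 0.93 |
| HR, equal 3-month lag for all | 1.00 | 1.00 |
| OR vs year-1 deaths, recoded (dropped) | 1.29 (1.23) | 1.29 (1.23) |
| OR vs all deaths, recoded | 1.06 | 1.09 |

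Varying the start rate from 0.5% to 5% per month widens the month-3 range to HR 0.91-0.97 and year-1 OR 1.15-1.29.

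**Step 5: what changes the size.**
- Later landmark, recoded: HR 0.965 and 0.95 at month 6; 0.98 and 0.97 at month 12 (0.985 with a start rate of 2% per month).
- Use from day 0, ever/never exposure: HR 1.00 at any landmark. If first dispensing falls within month 1 instead, HR is about 0.98.
- Use from day 0, amount of exposure: full-window use versus never gives HR 0.91 and 0.86 at month 3. Per month of use, HR is 0.98 and 0.97 at month 3, and 0.999 and 0.998 at month 12.
- Drug started because of dying (assumed in 30% of patients, on top of new starts): HR 1.07 and 1.11 without deletion, 0.94 and 0.91 with it (recoded), 1.00 with the equal lag.

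**Step 6: false leads.** Chance of a nominally significant protective HR (2.5% expected) with S5 = 20% and a month-3 landmark: at 20% exposed, 14% with N = 2,000, 22% with N = 4,079 and 82% with N = 20,000. At 5% exposed: 5.5%, 5.5% and 25%.

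**Step 7: control cohort.** With 5-year survival assumed at 80-90%, the same rule gives HR of about 0.97.

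**The case against.** The best defence has four parts.

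1. **The rule has a sound purpose.** It removes true end-of-life prescribing: without it, a drug started because of dying shows HR 1.07-1.11. That stands. But the rule overshoots to 0.94-0.91, whereas an equal lag lands on 1.00.

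2. **The bias is modest against the effect sought.** The design target of 20% versus 30% corresponds to HR ln(0.3)/ln(0.2) = 0.75 and OR (0.3/0.7)/(0.2/0.8) = 1.71, and the Discussion calls the effect sought very large. That stands for single estimates. It does not protect a screen that flags results at P=.05.

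3. **Many common drugs are already in use at diagnosis.** For ever/never exposure the bias is then small or nil after a landmark. That stands, but not for the quantitative exposure measures that are also planned.

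4. **Other safeguards exist.** The analyses are called exploratory, residual bias is admitted, and findings seen in controls are discarded. The control filter need not catch this artefact, because it is weaker where mortality is low. The caveat concerns what is left of the original biases, not one that the remedy adds. The Discussion speaks of shortening the time frame for each patient, which might hint at a lag for all, but the Methods define the window only relative to death.

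A reader might also infer more than the document supports:
- That the hazard is halved. An HR near 0.5 arises only within months 3-6, which the protocol does not analyse separately.
- That the rule favours every drug. Users from day 0 show no ever/never bias after a landmark.
- That decedents become never-users. The comparator wording allows that they are dropped instead.

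**Conclusion.** The point holds in a bounded form. The stated rule edits exposure only in those who die, and a drug with no effect started after diagnosis tends to look protective under either handling of the affected patients. The Cox bias is modest (HR about 0.91-0.97 at month 3, 0.95-0.97 at month 6, 0.97-0.985 at month 12). It is larger in the odds ratio against year-1 deaths (about 1.15-1.29), which is a sensitivity comparison, and smaller against all deaths (about 1.06-1.09).

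These sizes rest on constant hazard and assumed start patterns. The direction for new starts follows from the rule itself. The restriction to never-users raises a separate question, and its effect is not counted here.

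**What to change.** Keep the aim of removing end-of-life prescribing, but apply the gap to everyone whatever the outcome:

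- Count drugs dispensed up to a fixed date and start follow-up 3 months later in all patients alive then, for example exposure to month 3 and follow-up from month 6.
- Use the same patients and the same exposure definition for the odds ratios and for the Cox model, including the dose and duration measures.
- Vary the lag as a sensitivity analysis.

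In simulation the equal 3-month lag brings the HR under no effect back to about 1.00 at every landmark tried. The change costs one sentence in the protocol and an edit to the exposure code. The downside is that deaths during the lag leave the analysis set, so the results apply to patients who survive to the start of follow-up. The Results section says that analyses have begun, so the change should be made, dated and reported before candidate drugs are published.

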Hospital CMBD is a database in which diagnoses and procedures performed on hospitalized patients are recorded throughout the Spanish territory; all public hospitals and the majority of private hospitals (>95% hospital coverage) are included [14].Estació Clínica d'Atenció Primària (ECAP) is an electronic medical history program launched in 2001 and used by family doctors, pediatricians, and nurses from the Catalan Institute of Health (Institut Català de la Salut [ICS]) primary care centers when they visit patients; it includes all previous illnesses known to the primary care physician and records of the health care process in the outpatient setting, including assessments by health care personnel, diagnostic tests, and treatment, among others. The PADRIS program has only provided data since 2006, after which data are considered to be of good quality.The registry of causes of death is prepared by the INE using data from the Medical Certificate of Death or Statistical Bulletin of Death, Statistical Bulletin of Judicial Death, and Statistical Bulletin of Childbirth. It is prepared following the criteria established by the WHO (World Health Organization) in the International Classification of Diseases (ICD), which includes more than 12,000 diseases.Electronic prescription has been implemented in Catalonia progressively since 2010 and is currently deployed in 100% of primary care centers, pharmacies, and public hospitals in Catalonia. Prescribing and dispensing data will be obtained from the Comprehensive Health Information System of the Catalan Health Service (Servei Català de la Salut [CatSalut]), which is a computerized system used by the doctors of the national health system in Catalonia to prescribe financed pharmacological treatments to their patients and the pharmacies to dispense them; it contains information on the date of the prescription, the active ingredient, and dose, among other variables. Unfunded treatments can be prescribed using this tool but are often prescribed by other means (paper prescriptions).

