### Outcome Variables and Measurements

The primary end point is survival, calculated from the date of entry in the database until death or until 5 years of follow-up are reached. For patients in cohort 1, the earliest date of cancer diagnosis for which they have been selected to be part of the cohort will be considered the date of entry into the study (inclusion criterion).

As study variables, the following data will be collected from all patients:

List of diagnosed diseases (data source: CMBD and ICS ECAP diagnostic registry)Date of death (data source: INE cause of death registry)Cause of death (data source: INE cause of death registry)Pharmacological treatment (data source: Catalan electronic prescription), including all prescribed active ingredients, drug withdrawal dates from pharmacies, consumed doses, and prescribed regimen, during the entire follow-up periodSex (data source: Sistema Integral d'Informació de Salut)Date of birth (data source: Sistema Integral d'Informació de Salut)Basic health area (data source: Sistema Integral d'Informació de Salut)

For the patients included in the study with one of the cancers under study (cohort 1), the following variables will also be collected:

Type of cancer and presence of metastases (data source: CMBD and ICS ECAP diagnostic registry)Date of diagnosis for which the patient is included in the cohort (data source: CMBD and ICS ECAP diagnosis registry)Surgical treatment of the cancer (data source: CMBD)Date of surgical treatment (data source: CMBD)

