As a secondary objective, we plan to analyze the relationship between the presence of various nonneoplastic diseases and the survival of patients with cancer. To do this, we will compare the survival of patients with a specific disease to those who do not have it, adjusting multivariate models for age, gender, other conditions that may impact survival, and medications that have previously been shown to modify survival in previous analyses.

All analyses conducted in the cohort of patients with cancer will be replicated in a control patient group matched by age to the patients with cancer (with expected lower mortality) and in another group of older patients, where each control will be 10 years older than their cancer counterpart (with expected higher mortality). The findings that are reproduced in these groups of the control cohort will be discarded, as they are considered the result of uncontrolled biases or general effects on survival, not related to the cancers under study.

To consider a result statistically significant, the P value will be set at P=.05. All analyses are considered exploratory and hence subject to confirmation in new studies; therefore, no correction techniques will be applied to the P values obtained. All statistical analyses will be performed using R statistical software (version 4.1.0 or higher; R Core Team).

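### Exposure up to the landmark pools long-standing users with cancer-driven starters and can leave prior users who stopped among the unexposed, so an inert drug can show modest false harm or benefit

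*Protocol article*

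**What the plan says.** For cohort 1, Outcome Variables and Measurements sets time zero: "the earliest date of cancer diagnosis for which they have been selected to be part of the cohort will be considered the date of entry". The same section collects pharmacological treatment over the whole of follow-up. No period before entry is listed.

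Methods to Address Potential Sources of Bias then defines exposure among patients alive at a landmark, with month 3 as the example: "only drugs consumed at any time up to month 3 after the cancer diagnosis will be considered". In the comparison group, "only patients who have not consumed the drug at any point in their disease evolution will be taken into account". Patients who first take the drug after the cutoff are dropped.

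Three other provisions bear on the point:
- Reverse causality: "This bias will be alleviated by eliminating the drugs prescribed 3 months before death from the analysis".
- Confounding (Statistical Analysis): groups are matched on confounders. If imbalance or residual confounding is suspected, "adjustments for age, sex, and diagnostic groups will be performed".
- Cancer specificity (Statistical Analysis): "The findings that are reproduced in these groups of the control cohort will be discarded".

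The Discussion accepts that some effect of reverse causality and immortal time may remain in the analysed window, and expects it to be much smaller.

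**The concern.** The exposure definition sets no condition on when a drug was started. A patient on it for years and one given it last month for a complication of the tumour are both exposed. With no data before entry, a long-term user who stopped at diagnosis and never resumed looks like someone who never took it.

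The first months after a cancer diagnosis are when treatment lists change, and sicker patients may change more. Prognosis-related starting makes the exposed group sicker (false harm). Prognosis-related stopping moves sicker patients to the unexposed group (false benefit). False benefit is the signal a repurposing screen selects on.

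The stated safeguards address neighbouring problems. The landmark deals with immortal time. The reverse-causality rule acts near death, not near diagnosis. The control-cohort filter removes only findings that recur in people without cancer, who have no cancer-driven starts or stops, so such an artefact would pass as cancer-specific.

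**Working it through.** The protocol gives no figure for this bias, so its size has to be shown under assumptions.

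**Inputs from the protocol.** Pancreatic cancer, Table 2: 1,168 new cases a year and 8.2% 5-year survival. Diagnoses 2006 to 2012 give 1,168 × 7 = 8,176 patients. Landmark at month 3; 5% significance level.

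**Assumptions, not in the protocol.** The drug is inert; 40% have severe disease; 10% used the drug before diagnosis, independently of severity.
- Symptom drug: severe disease has HR 2; non-users start in months 0 to 3 in 20% (severe) v 5% (mild disease).
- Preventive drug: HR 2; users stop at diagnosis in 40% v 5%.
- Both: HR 2; these start and stop rates together.
- Mild assumptions: HR 1.5; starts 12% v 6%; stops 20% v 5%.

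**Step 1: how the groups become unbalanced.** Share with severe disease at time zero, before the landmark and the rule:
- Symptom drug, exposed: 0.4 × (0.1 + 0.9 × 0.20) = 0.112 severe; 0.6 × (0.1 + 0.9 × 0.05) = 0.087 mild; share 0.112/0.199 = 56%. Unexposed: 0.288/0.801 = 36%.
- Preventive drug, exposed: 0.4 × 0.1 × 0.60 = 0.024 severe; 0.6 × 0.1 × 0.95 = 0.057 mild; share 0.024/0.081 = 30%. Unexposed: 0.376/0.919 = 41%.
- Grouped by use before diagnosis: 40% in both groups.

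**Step 2: reach of the 3-month rule.** A drug started in month m is removed only if death comes before month m + 3. As m is at most 3, a start before the landmark always counts for anyone dying after month 6. The rule cannot act on a drug stopped at diagnosis.

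**Step 3: simulation.** Exponential survival calibrated to 8.2%, one-covariate Cox model from month 3 to year 5, 300 cohorts per scenario. Start times are uniform over months 0 to 3; a removed prescription counts as no exposure. Post-landmark starters are not modelled.

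| Scenario | HR without rule | HR with rule | Significant, with rule |
|---|---|---|---|
| Symptom drug | 1.14 | 1.08 | about 64% |
| Preventive drug | 0.93 | 0.94 | about 30% |
| Both | 1.11 | 1.05 | about 29% |
| Mild assumptions | 1.03 | 0.99 | about 5% |

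Grouping by use before diagnosis gives HR 1.00 with 2 to 6% significant throughout. The difference between 0.93 and 0.94 is simulation error.

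**Step 4: range.** A second simulation assumed 18% 5-year survival, half the patients at 2 to 3 times the hazard of the rest, and the rule applied:
- Starts 10% v 20%: HR 1.02 to 1.06. Starts 20% v 50%: HR 1.13 to 1.22.
- Stops 10% v 30%: HR 0.94 to 0.93. Stops 10% v 50%: HR 0.91 to 0.84.
- Starting unrelated to prognosis: HR 0.98 to 1.01.

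**Step 5: matching and cohort size.** With the rule, and stratification on a severity marker assumed 80% accurate, the four HRs become 1.03, 0.95, 1.01 and 0.98. With three diagnosis years (1,168 × 3 = 3,504) and no stratification, the symptom drug is significant in about 37% of cohorts and the preventive drug in fewer than 20%.

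**The case against.** Several objections have force.

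- **Severity is partly recorded.** A reader might infer that severity is absent from the data. It is not: metastases, surgery with its date, and all diagnoses are collected, and matching is planned. Histology and hospital cancer treatment are missing, as the Discussion says, and the named adjusters are only age, sex and diagnostic group. Step 5 shows that a reasonable marker shrinks the bias without removing it.
- **The rule near death helps.** A reader might take HR 1.14, significant in nearly every cohort, as the consequence of the plan. That ignores the protocol's own rule and uses all seven diagnosis years, although "Electronic prescription has been implemented in Catalonia progressively since 2010" and patients without prescription records are rejected. With the rule, roughly half of the false harm goes.
- **The exposure wording has no explicit lower bound.** It could be read to include use before diagnosis; the lower bound comes from the data-collection section. On that reading stopping matters less, but long-standing and new use are still pooled.
- **The authors concede a residual and call everything exploratory.** This is fair. But exploratory status excuses imprecision, not a systematic error that the specificity filter cannot see, and the expectation that the residual is much smaller is not supported by any figure.
- **Prior-use exposure is no cure-all.** It is null in the simulation because prior use was assumed unrelated to severity. Comorbidity can break that.

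**Conclusion.** The concern holds in a limited form. As written, the exposure definition and the collection window pool continuing users with cancer-driven starters, and prior users who stopped can count as never exposed. The landmark, the 3-month rule and the control cohort do not resolve this.

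The documents support that an inert drug can show false harm or benefit, not that it will. Direction and size depend on how starting and stopping relate to prognosis, which the protocol does not report. With the rule applied, the pancreatic example gives about HR 1.08 for a symptom drug, 0.94 for a preventive drug stopped in sicker patients, and 0.99 under mild assumptions. Stronger assumed dependence reaches 1.22 and 0.84. Capturing part of severity brings the estimates closer to 1.

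A reader might also conclude that use before diagnosis should become the lead exposure. The documents do not support that: with prescriptions phased in from 2010, a 12-month lookback leaves mainly diagnoses from 2011 and 2012, two of seven years (29%). The sample-size figure of 294 per group is unaffected.

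**What to change.** 1. Reconcile Outcome Variables and Measurements with Methods to Address Potential Sources of Bias: state whether use before diagnosis counts as exposure and, if so, over what period it is collected.
2. For patients with electronic-prescription lookback before diagnosis (mainly those diagnosed from about 2011), flag prior use. Report two separate contrasts beside the planned full-cohort analysis: prior users, kept in that group even if they stop, against patients with no prior use; and post-diagnosis starters against patients with no prior use.
3. Require a candidate drug's signal to hold in the prior-use contrast, or label it as open to reverse causality.
4. Include presence of metastases and surgery, both already collected, in the matching or adjustment set.

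**Cost.** One further extraction and one exposure flag. The separated contrasts cover a minority of diagnosis years, so they are less precise and should not replace the full-cohort analysis. A drug with few prior users may have no usable prior-use contrast and would then carry the label.

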### Duration

The patients in cohort 1 will have been diagnosed with the cancer under study between 2006 and 2012, both inclusive, and their survival will be retrospectively monitored for 5 years after diagnosis or until death if it occurs earlier. Cohort 2 will include patients without cancer who have had any type of contact with the health care system between 2006 and 2012, and these individuals will be followed up retrospectively for 5 years or until death if it occurs earlier.

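### The immortal-time rule defines its comparators by drug use after the landmark; if later starts are unrelated to prognosis, an inert drug looks protective

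*Protocol article*

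**What the plan says.** Under Methods to Address Potential Sources of Bias, the paragraph on immortal-patient bias has three steps.

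- The landmark. Among patients alive three months after diagnosis (given as an example), "only drugs consumed at any time up to month 3 after the cancer diagnosis will be considered".
- The removal. "Patients who consume the study drugs after the established time cutoff point will be eliminated from the analysis".
- The comparator. "As a comparison group, only patients who have not consumed the drug at any point in their disease evolution will be taken into account".

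The paragraph on reverse causality in the same section adds a rule on prescriptions shortly before death: "This bias will be alleviated by eliminating the drugs prescribed 3 months before death from the analysis". Under Duration, cohort 1 is followed so that "their survival will be retrospectively monitored for 5 years after diagnosis or until death if it occurs earlier". The Statistical Analysis section then compares exposed and unexposed patients for each drug, by exposure odds ratio and by Cox regression.

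**The concern.** The landmark alone is enough to remove immortal time: everyone has survived to month 3 and exposure is known by then. The next two sentences undo this. To be a comparator, a patient must avoid the drug from diagnosis to death or year 5, and the chance of avoiding it falls the longer the patient lives. Early deaths stay in the comparator group because they had no time to start the drug. Some long survivors are removed because they did have time. The paragraph opens by naming this mechanism, that longer survival brings more drug use, and the rule then lets it back in through the comparator.

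This rule governs the screen for the primary objective, so a bias here affects which drugs are put forward as candidates. Matching and adjustment for age, sex and diagnostic group cannot undo a selection made after time zero. The exploratory label and a possible false-discovery adjustment deal with chance, not with systematic bias.

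**Working it through.** **1. The plan's own figure.** The Sample Size Considerations section says it will be possible to "detect a difference of 10% between 2 groups with 294 individuals per group". With 20% against 30%, two-sided 5% and 80% power:

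n = [1.960·√(2·0.25·0.75) + 0.8416·√(0.2·0.8 + 0.3·0.7)]² / 0.10² = 293.2, rounded up to 294.

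The figure reproduces and is not in dispute. It serves below as a yardstick for study size.

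**2. Inputs.** From the protocol: landmark at 0.25 years, follow-up to 5 years (4.75 years after the landmark), and 5-year survival of 18.1% for lung (Table 2) or 20% (the stated maximum). Assumed, because the documents do not give them: a constant death hazard h, a constant start rate λ after the landmark that is unrelated to prognosis, and no drug effect.

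**3. Formulas.**

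- h = −ln(S5)/5. For lung, h = 1.7093/5 = 0.3419 per year.
- True survival from landmark to year 5, both groups: exp(−4.75h). For lung, 19.7%.
- Alive at year 5 and never started: a = exp(−4.75(h+λ)).
- Died before starting: d = [h/(h+λ)]·(1 − a).
- Apparent survival of never-users: a/(a+d).

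Worked case, lung, 2% per month (λ = 0.24): a = exp(−4.75·0.5819) = 0.063; d = 0.5875·0.937 = 0.550; a/(a+d) = 0.063/0.614 = 10.3%. The exposed group shows 19.7%. An inert drug appears to add about 9 points.

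**4. Inert drug at lung survival, under the protocol rule.** The HRs come from simulation; a range means that separate runs differed by simulation error.

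| Assumed start rate | Would start by year 5 if alive, 1 − exp(−4.75λ) | Never-users' apparent survival (true 19.7%) | HR |
|---|---|---|---|
| 2% per year | 9% | 18.8% | 0.96–0.97 |
| 0.5% per month | 25% | 17.0% | 0.88–0.92 |
| 1% per month | 43% | 14.5% | 0.80–0.82 |
| 2% per month | 68% | 10.3% | 0.67–0.68 |

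With later starters kept as unexposed, the HR is 0.98–1.02.

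**5. False positives with 294 per group, 20% survival, inert drug, 4000 simulated studies.** At 0.02, 0.05, 0.10 and 0.20 starts per year, the rule gives a median HR of 0.96, 0.91, 0.84 and 0.71. A falsely significant protective result appears in 6%, 16%, 48% and 97% of studies (nominal 2.5%). The plain landmark gives a median HR of 1.00 and two-sided rejection of 4.8% to 5.4%. The spurious odds ratios for 5-year survival at the same rates are 1.06, 1.16, 1.36 and 1.87, so the odds-ratio approach is affected too.

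**6. Direction.** If 10% to 30% of patients start late and those starts fall 3 to 12 months before death, the same rule gives an inert drug an HR of 1.04 to 1.16. If the removal sentence also excludes early users who continue, early deaths are selected into the exposed group and the HR is 1.4 to 3.6 in the scenarios run.

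**7. Control cohort.** With assumed 5-year survival of 70% to 90% and 0.10 starts per year, the artefact gives an HR of 0.78 to 0.81 in controls.

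**8. Companion rule.** Ignoring prescriptions in the last three months of life also uses future information. At 10% survival and 0.10 starts per year, adding it moves the HR under the protocol rule from 0.85 to 0.79. It moves the plain landmark from 0.99 to 0.92.

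**The case against.** The strongest case on the other side has four parts.

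*Direction.* A reader might infer that the rule always favours the drug. The documents do not support that. The protocol itself says that some drugs are prescribed because death is near, and such late starts reverse the sign. The removal sentence speaks of patients who consume the drug after the cutoff, not of patients who start it then. Read literally, it also selects within the exposed group, and in the opposite direction. This objection stands as to direction. It does not rescue the rule, because either reading conditions on the future.

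*Size.* The start rates are assumptions. The study screens all available drugs, and many will be started rarely after diagnosis. At about 2% per year the bias is small. This stands: the bias is material only for drugs that are started fairly often.

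*Safeguard.* A reader might infer that the artefact would dominate the list of protective candidates. That ignores the control-cohort filter in the Statistical Analysis section, which discards findings that recur in people without cancer. Since the artefact arises there too, many false candidates may be discarded. The filter is still not a cure. A real effect that appears alongside the artefact in controls may be discarded with it, and the artefact can pass where start rates differ between cohorts.

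*Acknowledgement.* The Discussion concedes residual immortal-patient bias and calls for confirmation in later studies. But it places the residual effect within the retained time window and expects it to be much smaller. It does not mention the comparator rule.

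**Conclusion.** The point holds. The rule as written selects comparators on exposure after time zero, and following it gives a biased comparison even for a drug with no effect. If later starts are unrelated to prognosis and the removal sentence means later starters, the bias is protective. Its size then runs from small (HR about 0.97 at 2% starts per year) to an HR of about 0.68 with a survival gap of about 9 points (2% per month), close to the 10-point difference used for sizing. These sizes rest on assumed start rates and a constant hazard; a decreasing hazard (Weibull shape 0.7) gave similar or slightly larger odds ratios. Neither a uniformly protective direction nor a candidate list made up mainly of artefacts is established.

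**What to change.** - Delete the removal sentence and the comparator sentence. Classify each patient once, by dispensing up to the landmark. Keep patients who start later in the unexposed group and follow everyone from the landmark.
- If any removal of post-landmark users is kept for a sensitivity analysis, say whether it means patients who start the drug then or all who consume it.
- Do not let the three-months-before-death rule alter the landmark classification, since that uses the date of death to define exposure.
- As a sensitivity analysis, use Cox regression with time-dependent exposure, lagged from first dispensing so that drugs started because death is near do not bring back reverse causality.
- Apply the same definitions in the control cohort. The Results section says analyses have begun, so rerun any already made under the present rule.

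The cost is a short text edit and a change of analysis code. No new data are needed and more patients are kept. The downside is some dilution toward the null, because later starters count as unexposed.
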